#### 27b – Analysis methods – adjustment for covariates

- Principal outcome analyzes (secondary objectives) :

The reviewer of the manuscript proposed to complete the analysis with a linear regression that adjusts for baseline pain score and site (as a stratification variable) to give a more precise treatment effect estimation.

#### 27c – Analysis methods –assumptions to be checked

The parameters normality will be checked using Shapiro Wilks test.

The variances homogeneity will be checked using test on the equality of standard deviations.

#### 27d – Analysis methods – alternative methods

- Principal outcome analyzes :

The reviewer of the manuscript proposed to complete the analysis with a linear regression that adjusts for baseline pain score and site (as a stratification variable) to give a more precise treatment effect estimation.

- Principal outcome analyzes (complementary analysis) :

The superiority of intra-nasal Sufentanil compared to the reference treatment will be evaluated using a two sample Student t test after verification of the application conditions.

However, in the case where the application conditions were not respected, a non-parametric Mann-Whitney test, considered robust, was considered as a possible alternative.

- Secondary outcome analyzes (secondary objectives) :

- The objective n°2 is to compare the efficacy of analgesia performed by intranasal Sufentanil compared to the reference treatment (IV Morphine) after 10 min and 20 min of treatment.

The efficacy of intra-nasal Sufentanil compared to the reference treatment will be evaluated using a non-parametric Mann-Whitney test, considered robust, when the application conditions of the two group Student t test will not be respected.

- The objective n°3 is to evaluate the efficacy of analgesia performed by intranasal Sufentanil and Morphine IV, after 10 min and 20 min of treatment.

The comparative analysis of the measurement of the numerical scale of the pain (10 or 20 min) compared to baseline will be performed using a non-parametric Wilcoxon test when the application conditions of the Student's test for paired series will not be respected.

- The objective n°4 is to compare the occurrence of adverse effects between treatment groups (Sufentanil IN versus Morphine IV).

The comparative analysis of the adverse effects between treatment groups (Sufentanil IN versus Morphine IV) will be performed using an exact Fisher test when the expected value of a contingency table cell will be less than 5.

- The objective n°5 is to evaluate the feasibility in pre-hospitalized patients.

The comparative analysis of patient satisfaction will be performed using a non-parametric Mann-Whitney test when the normality or homogeneity of the variances is rejected.

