##### **Version 2.0 of April 29, 2014 [name] (Protocol version 8.0 – 29/04/2014):**

This study will involve a sample size of 198 patients (99 patients per group). In order to guarantee this number of analyzable patients, we envisage a complementary recruitment of 10 patients per group. The calculation of the number of patients required corresponds to a non-inferiority study design.

The null hypothesis corresponds to a difference in efficacy between treatment groups above the equivalence threshold; The alternative hypothesis allows us to conclude that the treatments are equivalent;

The primary endpoint is the difference, before / after, of the mean pain score assessed by a numerical scale at inclusion and 30 minutes after administration.

The number of subjects required was assessed by the Schuirmann method, taking into account a minimal, clinically significant value of pain level evolution defined a priori as a modification of 1.3 of the numerical scale (EN), an alpha risk of 2.5% and a standard deviation of the response of 2.8.

A total of 99 subjects per group will thus be necessary to reject the null hypothesis of a difference in efficacy and to conclude that the evaluated treatment is not inferior compared to the reference treatment, in terms of the evolution of EN in the first 30 minutes, with a power of 80%.

This calculation was performed using the NQuery Advisor software version 7.0 (Statistical Solutions Ltd., Boston MA, USA).

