### 27a – Analysis methods - presentation

- Principal objective analysis :

The main objective is to compare the efficacy of analgesia after 30 min performed by intranasal Sufentanil compared to the reference treatment (Intravenous Morphine).

Outcome: The analysis criterion corresponds to the variation of the numerical scale of the pain (EN at T30 – EN at T0) between the reference treatment (Morphine IV) and the tested treatment (Sufentanil IN).

Population of analysis: The analysis of the main objective will focus on the per-protocol (PP) population, that is to say on all patients included hospitalized in emergencies without major violation to the protocol integrating in particular patients who received the treatment dose provided for in protocol.

Analysis: The non-inferiority of the study treatment compared to the reference treatment in terms of variation of the numerical scale of pain (EN at T30 – EN at T0) will be evaluated using a one sided mean-equivalence t test on the per protocol population. We used the TOSTT procedure (*Dinno A. 2015. tostt: mean-equivalence t tests, Stata software package*) that tests the equivalence of means in a symmetric equivalence interval using the two-tailed unilateral test approach (Schuirmann 1987).

The equivalence threshold corresponds to the minimal, clinically significant, change in the level of pain; It has been defined a priori as a modification of 1.3 of the numerical scale (EN).

The statistical threshold of significance will be  $p < 0.025$ .

- Secondary objectives analysis :

- The objective n°2 is to compare the efficacy of analgesia performed by intranasal Sufentanil compared to the reference treatment (IV Morphine) after 10 min and 20 min of treatment.

Outcome: The analysis criterion corresponds to the variation of the numerical scale of the pain (EN at T10 or T20 – EN at T0) of each treatment (Sufentanil IN versus Morphine IV).

Population of analysis: The analysis will be carried out on the per-protocol (PP) population and then on the intention-to-treat (ITT) population of patients hospitalized in the emergency department.

Analysis: The evaluation of the efficacy of analgesia of pain at intermediate times will be carried out between treatment groups.

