#### 28 – Missing Data

##### - Recoding Primary criteria:

Implementation of the modified ITT analysis required the replacement of missing data; this was performed using the multiple imputation method. Ten imputations of the missing data were taken into account in the multiple imputation process.

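### Pre-tests for normality and equal variances choose between Student and Mann-Whitney at T10/T20, and may do so for superiority, moving a mean-based plan onto a rank hypothesis with no named estimate

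*SAP*

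**What the plan says.** Section 27c sets two checks: "The parameters normality will be checked using Shapiro Wilks test", and "The variances homogeneity will be checked using test on the equality of standard deviations". It gives no significance level for either and does not say whether they are run by arm or on pooled data.

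Section 27d attaches consequences:

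- **Superiority at T30.** Student's test is planned. If its conditions fail, "a non-parametric Mann-Whitney test, considered robust, was considered as a possible alternative". This permits a switch but does not require one.
- **Objective 2 (T10 and T20).** Mann-Whitney will be used "when the application conditions of the two group Student t test will not be respected". This is an instruction.

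The primary analysis has no rank fallback. In section 27a, non-inferiority "will be evaluated using a one sided mean-equivalence t test on the per protocol population". The margin is a mean change, "defined a priori as a modification of 1.3 of the numerical scale (EN)".

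Section 29 makes superiority the hierarchical step after non-inferiority, on the ITT population, two-sided at 5%. Section 28 describes imputation of the primary criterion: "Ten imputations of the missing data were taken into account in the multiple imputation process". The same section plans no replacement of missing data for secondary criteria. In Appendix I, Tables 2 and 3 show mean differences with 95% CI and a Student p-value. Neither has a place for a rank result.

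**The concern.** Non-inferiority and superiority are two steps on one variable, the change in EN from T0 to T30. The first is stated in mean points against 1.3. If the second moves to Mann-Whitney it tests a different hypothesis, which coincides with a mean difference only under an extra assumption such as a pure shift. The plan names no estimate to accompany it, so a rank p-value could stand beside a mean CI that points the other way.

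The trigger is also poorly matched to the problem. Shapiro-Wilk reacts to the ties of a coarse score, which hardly affect a t test with this many patients per arm. Unequal variance may be the other trigger, and Mann-Whitney is no remedy for that.

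For superiority two more things are unsettled: who decides whether to use the optional alternative, and how ten Mann-Whitney results are to be combined, including when the pre-tests pass in some imputed data sets and fail in others.

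**Working it through.** **1. The plan's own figure.** Section 11 (version 2.0) uses margin 1.3, "an alpha risk of 2.5% and a standard deviation of the response of 2.8", and 80% power, giving 99 per group. With two one-sided tests and a true difference of 0:

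n = 2 × SD² × (z₀.₉₇₅ + z₀.₉₀)² / margin² = 2 × 2.8² × (1.960 + 1.282)² / 1.3² = 97.5, so 98 by the normal approximation.

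With the t distribution, power is 0.797 at 98 and 0.803 at 99, so 99 is reproduced. The trial is sized on a difference in means.

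**2. Inputs for the switch rate.**

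- From the SAP: SD 2.8 (design) and 2.1 (section 11, post-hoc paragraph); T30 mean 3.7 with SD 2.2 under morphine (section 11, version 1.0); entry EN of at least 6 (section 22); a scale out of 10 (Table 1 template); 99 per arm.
- Assumed: whole-number scoring; pre-tests in each arm; a pre-test level of 5%, with 2.5% as an alternative because section 16 names that threshold for statistical tests in general; n = 60 as a lower case, since section 11 says recruitment fell short without giving a number; the T0 distribution and the T0–T30 correlation.

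**3. What fires by chance alone.** With continuous normal data, two Shapiro-Wilk tests and one variance test at 5% give about 1 − 0.95³ = 0.14; simulation gave about 0.15.

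**4. What fires with whole-number scores and identical arms.** At SD 2.1 and n = 99, Shapiro-Wilk rejected in one arm in 0.810 of trials and the variance test in 0.048. If independent, 1 − (1 − 0.810)² × (1 − 0.048) = 0.966; the simulated rate was 0.961. At SD 2.8: 1 − (1 − 0.323)² × (1 − 0.045) = 0.562, simulated 0.558.

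Simulated proportion of trials in which a pre-test rejects:

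| Change score | Shapiro-Wilk form, level | n = 99 | n = 60 |
|---|---|---|---|
| Rounded normal, SD 2.1 | usual, 5% | 0.96 | 0.66–0.69 |
| Rounded normal, SD 2.8 | usual, 5% | 0.56–0.59 | 0.34–0.37 |
| T0 of 6–10, T30 mean 3.7, SD 2.2 | usual, 5% | 0.96 | 0.63–0.65 |
| Narrower, T10-like change | usual, 5% | 1.00 | 1.00 |
| Rounded normal, SD 2.1 | usual, 2.5% | 0.82 | 0.42 |
| Rounded normal, SD 2.8 | usual, 2.5% | 0.34 | 0.18 |
| All whole-number scenarios | tie-averaged, 5% | 0.35–0.70 | 0.33–0.56 |

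The overall range is 0.18 to 1.00.

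**5. Does the t test need rescuing?** On equal whole-number scores at n = 99, its two-sided type I error was 0.044–0.051 against 0.05. Choosing the test by pre-test gave 0.04–0.07. With SD 2.8 against 2.1 and 99 per arm, the error rates were 5.3% (Student), 5.3% (Welch) and 5.4% (Mann-Whitney), so the switch repairs nothing.

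**6. How often does the choice alter the verdict?** Student and Mann-Whitney disagreed on significance in about 1–3% of trials with no difference, and in about 0–9% with an assumed shift of 0.85 points.

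**7. Power at that shift, n = 99.** Student against Mann-Whitney: 0.81 against 0.78 at SD 2.1; 0.58 against 0.55 at SD 2.8.

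**The case against.** The best defence is that little changes in practice. The two tests usually agree, the error rate stays near its nominal value, and only superiority and secondary results are touched. The templates keep the mean difference and its CI whichever test supplies the p-value, and no section removes them. Sections 27b and 27d also add a regression adjusted for baseline pain and site. All of this stands, and it limits the point to clarity of hypothesis and freedom of choice.

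The switch rates also depend on assumptions that the SAP does not settle, which is why a wide range is given and not one figure.

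A reader might infer more, but the document does not support it:

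- **That superiority will be switched whenever a pre-test rejects.** The superiority wording is permissive. An explicit rule about rejecting normality or homogeneity appears in 27d only for patient satisfaction.
- **That the imputed analysis becomes impossible.** A rank-based estimate with a standard error could be pooled. The gap is that the SAP names neither the estimate nor the rule. The non-inferiority test on imputed data is untouched.
- **That imputation is also a problem at T10 and T20.** Section 28 excludes secondary criteria from imputation.
- **That false-positive rates are inflated.** An unequal-SD example with clearly unequal arms would show slight inflation, but it does not fit a 1:1 trial analysed by ITT, and in such an example Student fares no better than Mann-Whitney.

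**Conclusion.** The point holds in limited form. Sections 27c and 27d let pre-tests of unstated level select the test, by instruction at T10 and T20 and as an open option for superiority. Under whole-number scoring and testing by arm, rejection would occur in roughly 20% to nearly 100% of trials even when the arms are identical. Mostly this reflects the coarseness of the scale and not a failing t test.

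The consequence is a data-dependent hypothesis without a named effect estimate, a p-value that may not match the mean CI in Tables 2 and 3 and, for superiority only, no combination rule over ten imputations. The primary non-inferiority conclusion is not affected. This is worth correcting because the correction is so cheap; it does not threaten the main result.

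**What to change.** In 27c and 27d, stop using the pre-tests to select the test; distributions can still be described.

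For superiority and objective 2, always report the mean difference with its 95% CI. Either Welch's test or the baseline- and site-adjusted regression already in 27b and 27d would serve, provided one is named as the main analysis. Section 4a shows that the regression entered in May 2019 during manuscript review, so Welch is the closer relative of the test first planned.

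For the imputed T30 superiority analysis in ITT, state that the estimate and its standard error are pooled by Rubin's rules. Do not extend this to objective 2, whose data section 28 leaves unimputed.

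Keep Mann-Whitney as a sensitivity analysis that does not decide the conclusion.

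The cost is a few sentences, with no notable loss of power in the scenarios examined. Tables 2 and 3 keep their layout; only the footnote naming the test needs to match the choice.

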#### 27e – Analysis methods – planned subgroup analyses

No subgroup analysis is considered for the randomized trial analysis.

#### 28 – Missing Data

##### - Recoding Primary criteria:

Implementation of the modified ITT analysis required the replacement of missing data; this was performed using the multiple imputation method. Ten imputations of the missing data were taken into account in the multiple imputation process.

##### - Recoding Secondary and exploratory criteria:

No data replacement was considered.

#### 29 – Additional analyses

- Principal outcome analyzes (sensitivity analysis) :

Sensitivity analysis of the primary objective: The evaluation of the non-inferiority of intra-nasal Sufentanil compared to the reference treatment conducted on the per-protocol population (PP) will be confirmed on the intention-to-treat population (ITT) in sensitivity analysis to comply recommendations of the guidelines (JAMA, 2012). This will be evaluated using a Schuirmann test on the imputed data. This analysis will retain the 2.5% as the statistical threshold.

In practice for a more robust result, both analyzes (PP and ITT) must be performed and give similar results.

- Principal outcome analyzes (complementary analysis) :

The evaluation of the superiority of intra-nasal Sufentanil compared to the reference treatment is used in hierarchical analysis. This will be evaluated on the intention to treat analysis using a two sample Student t test after verification of the application conditions.

Although unilateral testing appears to be most consistent with therapeutic hypotheses, we used a two-sided test. By decreasing the risk of alpha error on the conclusion of superiority, a two-sided test is more conservative.

This analysis will retain the 5% as a statistical threshold. This analysis will not require adjustment of the statistical threshold.

### 30 – Harms

The safety data will be summarized by the frequency of events.

### 31 – Statistical software

Statistical analysis will be performed using STATA® Software Version 14.2 or higher (Stata Corporation [name]).

### 32a – References – for non-standard statistical methods

Not applicable

### 32b – References to Data Management Plan

The data consistency check was performed during the data entry on Redcap and the blind review preparation.

### 32c – References to the Trial Master File

The Clinical Research Department (DRCI) of the University Hospital Center of Grenoble Alps (CHUGA) was in charge of maintaining and storing documents related to the “Algofine-2” clinical trial.

The Trial Master File is available from the DRCI under the reference 38RC13.558 ; This information is archived on the DRCI server.

## 7. Appendix I

### Template of table of descriptive analysis at the inclusion visit

| Table 1 – Baseline characteristics of participants |                   |                                                                           |
|----------------------------------------------------|-------------------|---------------------------------------------------------------------------|
|                                                    |                   | 
Groupe 1
 
n=XXX
 
Groupe 2
 
n=XXX
 |
| Age                                                | median [IQR]      |                                                                           |
| Gender (Men)                                       | Frequency(number) |                                                                           |
| Weight                                             | median [IQR]      |                                                                           |
| Trauma area                                 |                   |                                                                           |
| Head                                               | Frequency(number) |                                                                           |
| Shoulder                                           | Frequency(number) |                                                                           |
| Arm / elbow                                        | Frequency(number) |                                                                           |
| Wrist or hand                                      | Frequency(number) |                                                                           |
| Thorax wall                                        | Frequency(number) |                                                                           |
| Rachis                                             | Frequency(number) |                                                                           |
| Pelvis / hip                                       | Frequency(number) |                                                                           |
| Leg / knee                                         | Frequency(number) |                                                                           |
| Ankle or foot                                      | Frequency(number) |                                                                           |
| Vital Parameters at inclusion               |                   |                                                                           |
| HR(per min)                                        | median [IQR]      |                                                                           |
| RR (per min)                                       | median [IQR]      |                                                                           |
| SpO 2 (%)                               | median [IQR]      |                                                                           |
| MAP (mmHg)                                         | median [IQR]      |                                                                           |
| NRS (/10)                                          | median [IQR]      |                                                                           |
| Co-analgesia                                |                   |                                                                           |
| Paracetamol                                        | Frequency(number) |                                                                           |
| Codeine                                            | Frequency(number) |                                                                           |
| Ketoprofen                                         | Frequency(number) |                                                                           |

Templates of table of the principal outcomescales analysis between the inclusion (T0) and the visit at T30 and between groups.

| Table 2 – Criteria between T0 and T30                                                                                                       |                    |                    |                                                             |                           |
|---------------------------------------------------------------------------------------------------------------------------------------------|--------------------|--------------------|-------------------------------------------------------------|---------------------------|
| Scale EN                                                                                                                                    | Group 1
(n=XXX) | Group 2
(n=XXX) | Delta G1-G2
mean $\pm$ se [IC95%]
Effect Size [IC95%] | p
value                |
| Delta EN T30-T0                                                                                                                             | mean $\pm$ SD      | mean $\pm$ SD      | mean $\pm$ SD [CI],
Cohen's d Effect Size [CI]           | P
value  |
| Results expressed as mean $\pm$ standard deviation [95% CI], Cohen's d Effect Size [95% CI]
(5) p based on an Student two sample T test. |                    |                    |                                                             |                           |

Templates of tables of scales analysis between the inclusion (T0) and the visit at T10 or T20 and between groups.

| Table 3 – Criteria between T0 and T10 or T20                                                                |                    |                    |                                         |                           |
|-------------------------------------------------------------------------------------------------------------|--------------------|--------------------|-----------------------------------------|---------------------------|
| Scale EN                                                                                                    | Group 1
(n=XXX) | Group 2
(n=XXX) | Delta G1-G2
mean $\pm$ se
[IC95%] | p
value                |
| Delta EN T10-T0                                                                                             | mean $\pm$ SD      | mean $\pm$ SD      | mean $\pm$ SD [CI],
[IC95%]          | P
value  |
| Delta EN T20-T0                                                                                             | mean $\pm$ SD      | mean $\pm$ SD      | mean $\pm$ SD [CI],
[IC95%]          | P
value  |
| Results expressed as mean $\pm$ standard deviation [95% CI]
(5) p based on an Student two sample T test. |                    |                    |                                         |                           |

Templates of tables of scales analysis between the inclusion (T0) and the visit at T10 by groups.

| Table 4 – Criteria between T0 and T10                                                                          |               |               |                                     |                        |
|----------------------------------------------------------------------------------------------------------------|---------------|---------------|-------------------------------------|------------------------|
| Scale EN                                                                                                       | T0            | T10           | Delta T10-T0
Effect Size [IC95%] | p
value             |
| Groupe 1
(n=XXX)                                                                                     | mean $\pm$ SD | mean $\pm$ SD | mean $\pm$ SD [CI],
[IC95%]      | P value  |
| Groupe 2
(n=XXX)                                                                                     | mean $\pm$ SD | mean $\pm$ SD | mean $\pm$ SD [CI],
[IC95%]      | P value  |
| Results expressed as mean $\pm$ standard deviation [95% CI]
(5) p based on an Student paired sample T test. |               |               |                                     |                        |

Templates of tables of scales analysis between the inclusion (T0) and the visit at T20 by groups.

| Table 5 – Criteria between T0 and T20                                                                      |           |           |                                     |                        |
|------------------------------------------------------------------------------------------------------------|-----------|-----------|-------------------------------------|------------------------|
| Scale EN                                                                                                   | T0        | T20       | Delta T20-T0
Effect Size [IC95%] | p
value             |
| Groupe 1
(n=XXX)                                                                                 | mean ± SD | mean ± SD | mean ± SD [CI],
[IC95%]          | P value  |
| Groupe 2
(n=XXX)                                                                                 | mean ± SD | mean ± SD | mean ± SD [CI],
[IC95%]          | P value  |
| Results expressed as mean ± standard deviation [95% CI]
(5) p based on an Student paired sample T test. |           |           |                                     |                        |

Template of table of adverse event analysis between groups.

| Table 6 –Adverse events observed                                      |                    |                    |            |
|-----------------------------------------------------------------------|--------------------|--------------------|------------|
|                                                                       | Groupe 1
n=XXX  | Groupe 2
n=XXX  | p
value |
| Severe adverse events                                          | number (Frequency) | number (Frequency) | p value    |
| Hypoxemia (SpO 2 <90%)                                     | number (Frequency) | number (Frequency) | p value    |
| Hypotension (SBP <90 mmHg)                                            | number (Frequency) | number (Frequency) | p value    |
| Bradypnea (RR <10/min)                                                | number (Frequency) | number (Frequency) | p value    |
| Anaphylactic shock                                                    | number (Frequency) | number (Frequency) | p value    |
| Alteration of consciousness (Ramsay>2)                                | number (Frequency) | number (Frequency) | p value    |
| Bradycardia (bpm<45/min)                                              | number (Frequency) | number (Frequency) | p value    |
| Naloxone use                                                          | number (Frequency) | number (Frequency) | p value    |
| Mild adverse events                                            | number (Frequency) | number (Frequency) | p value    |
| Dizziness                                                             | number (Frequency) | number (Frequency) | p value    |
| Hot flushes                                                           | number (Frequency) | number (Frequency) | p value    |
| Nausea or vomiting                                                    | number (Frequency) | number (Frequency) | p value    |
| Bad taste / smell                                                     | number (Frequency) | number (Frequency) | p value    |
| Mild allergic reaction                                                | number (Frequency) | number (Frequency) | p value    |
| Epistaxis / Rhinorrhea                                                | number (Frequency) | number (Frequency) | p value    |
| Hallucinations                                                        | number (Frequency) | number (Frequency) | p value    |
| Results expressed in number (Frequency),
Chi2, Fisher's exact test |                    |                    |            |

